## 7.3 SAE reporting

In case an adverse event meets the seriousness criteria (see section 7.1) the SAE-Reporting-Form, as filed in the ISF, has to be filled out. Details about the process are specified on this form.

## 7.4 Suicidality

Suicidality will be assessed at the screening visit and at every following visit via clinical interview conducted by the rater and during the assessment of serious adverse events and adverse events. In addition, cut-off thresholds in the HRSD-24 (Item 3 > 1) and BDI-II (Item 9 > 1) are checked. In case of suicidality, the rater has to determine the risk level: At low risk, the patient has passive suicidal ideations, but no suicidal intentions, plans or active wish to commit suicide. All study personnel should pay attention to suicidality and assess the change of status carefully at every

visit. The patient must be informed about help services and emergency plans in case of worsening of symptoms.

At increased risk, the patient has suicidal intentions or plans, but no active wish to commit suicide. This is an urgent situation. The study personnel have to ensure that the patient is being seen by a psychiatrist within 24 hours. The patient must be informed about help services and emergency plans in case of further worsening of symptoms.

At acute risk, the patient has active suicidal intentions or plans. Self-control or external social support might be lacking (e.g. family, friends) or be unclear. The study personnel must immediately initiate the admission of the patient to a psychiatric inpatient unit.

## **8 Data Collection and Management**

### **8.1 Data confidentiality**

Information about trial patients will be kept confidential and managed under the applicable laws and regulations. Those regulations require a signed patient authorisation informing the patient of the following:

- which protected health information (PHI) will be collected from patients in this trial;
- who will have access to that information and why;
- who will use or disclose that information;
- the rights of a research patient to revoke their authorisation for use of their PHI.

In the event that a patient revokes authorisation to collect or use PHI, the investigator, by regulation, retains the ability to use all information collected prior to the revocation of patient authorisation. For patients that have revoked authorisation to collect or use PHI, attempts should be made to obtain permission to collect at least vital status (i.e. that the patient is alive) at the end of their scheduled trial phase.

The data collection system for this trial uses built-in security features to encrypt all data for transmission in both directions, preventing unauthorised access to confidential participant information. Access to the system will be controlled by individually assigned user identification codes and passwords, made available only to authorised personnel who have completed prerequisite training.

### **8.2 Documentation of trial data**

#### **8.2.1 Documentation in medical records**

The investigator will record the participation in the trial, the frequency of the trial visits, the relevant medical data, the concomitant treatment and the occurrence of adverse events in the medical record of each trial patient.

#### **8.2.2 Documentation in (e)CRF**

An electronic data capture (EDC) system will be used in this trial. All data collected during the trial will be entered on the trial-specific e-forms by the responsible investigator, or designated person, as timely as possible. Data entry and data corrections on e-forms are automatically tracked in the audit trail created by the EDC system. The investigator, or a deputy who is designated by the investigator, will document the trial data in the eCRF as promptly as possible, but not later than two weeks after patient's visit.

Data corrections in the e-CRF due to queries are performed by the responsible investigator, or designated person, as timely as possible.

### **8.3 Data management**

The data management will be performed with REDCap™, a fully web based remote data entry system based on web forms, which is developed and maintained by the REDCap™ Consortium (<https://projectredcap.org/about/consortium/>).

The technical specifications of the database will be described in the codebook delivered automatically by the REDCap™ system.

Details on data management (software, procedures, responsibilities, etc.) will be described in a data management manual prior to the trial. During the trial, the performance of data management and any deviations from the data management manual will be documented. Technical specifications of the trial data base and all data checks will be documented in the Study Data Dictionary and Codebook.

The trial data base has been fully validated before any data entry will be performed. Data entry personnel will not be given access to the trial data base until they have been trained. An audit trail provide a data history which data were entered, changed or deleted, by whom and when.

Data will be checked during data entry by so-called edit checks. If applicable, the data will be reviewed for completeness, consistency, plausibility, and regarding protocol violations and other distinctive problems (e.g. cumulative missings) using SAS software. The resulting queries will be sent to the investigator at the site for correction or verification of the documented data. The queries should be completed within 14 days.

All programmes which can be used to influence the data or data quality will be validated (e.g. edit check and data validation programmes, programmes for eCRF/query tracking or for import of external data, etc.).

### **8.4 Data coding**

Concomitant medications entered into the database will be coded using the WHO Drug Reference List. Concomitant therapies will be described based on a study-specific pre-specified list.

Medical history/current medical conditions will not be coded. A study-specific pre-specified list of categories will be used in the eCRF.

Adverse events will be categorised as specified in section 7.1.

## **9 Quality Assurance System**

During the study, quality control and quality assurance will be ensured through monitoring, auditing and supervision by the authorities.

### **9.1 Quality Control (Monitoring)**

The investigators at all trial sites will grant the CRA access to the patients' personal medical records for the verification of the proper documentation of study data. The provisions of the Federal Data Protection Act will be fully observed (the CRA is bound by medical secrecy when comparing the CRFs with the source documents).

All investigators agree that the CRA will visit the centre before, during and after completion of the study. The investigator must allow sufficient time for these visits, alternatively the CRA may be provided with other trained staff for assistance during the visits. The investigator will grant the CRA access to the source documents for the fulfilment of his/her duty. The aim and purpose of these visits is, in particular:

- evaluation of the progress of the study,

- check for compliance with the study protocol,
- CRF review for accuracy and completeness,
- CRF validation against source data,

A monitoring reports will be written on each visit. This will document the progress of the study and give an account of all problems that occurred (e.g. refusal of inspection).

Between visits, the responsible CRA will maintain regular telephone contact with the study centres. Further detailed information on monitoring will be recorded in a monitoring plan.

## **9.2 Source Data Verification (SDV)**

Source data verification will be performed in order to verify the accuracy and completeness of the entries on the case report form (CRF) by comparing them with the source data, and to ensure and increase the quality of the data. All data which are patient to SDV must have been entered in the medical record or, in the case of source documents, enclosed with the medical record. The investigators will afford the CRA access to the medical records for the performance of SDV.

Source data as defined by ICH-GCP include data such as hospital records, clinical and office charts, laboratory notes, memoranda, patients' diaries or evaluation checklists, pharmacy dispensing records, recorded data from automated instruments, copies or transcriptions certified after verification as being accurate copies, microfiches, photographic negatives, microfilm or magnetic media, x-rays, and records kept at the pharmacy, at the laboratories and at medico-technical departments involved in the clinical study.

## **9.3 Quality Assurance (Auditing)**

According to the ICH-GCP guidelines, audits will be performed according to a quality assurance system. These may be conducted by the coordinating investigator, the Medical Center Freiburg or by an authority.

During an audit, the planning, conduct and analysis of a study will be checked for compliance with the national laws and the requirements of the ICH-GCP guidelines.

This includes checking the data management and organisation at the study site and inspecting institutions, laboratories and source documents. The aim of quality assurance is to ensure that the results and conclusions described in the final report can be correctly deduced from the raw data.

All persons who conduct an audit undertake in writing to treat all data which are patient to medical secrecy or could reveal the patient's identity in absolute confidence, and to restrict the use of such data to the purposes agreed by the patient in writing.

Proposed audit dates, characteristics of the selected patients and further information will be transmitted to the investigator by the CRA in a timely manner.

# **10 Biostatistical Planning and Analysis**

Before the start of the final analysis a detailed statistical analysis plan (SAP) will be prepared. If the SAP contains any changes to the analyses outlined in the trial protocol, they will be marked as such, and reasons for amendments will be given.

All statistical programming for analysis will be performed with the Statistical Analysis System (SAS) or R.

## **10.1 Trial Design**

For details on trial design see section 3.1 of the protocol.

## 10.2 Blinding of study statistician

A member of the CTU who is not involved in the trial will produce programme code to generate randomisation lists providing allocation of patient groups of size 4-6 to the IPT-Work or SP condition. The study statistician will provide the details for the implementation of the randomisation lists, which will be stratified by centre, in blocks of variable length with a 1:1 ratio, in a document which will not be disclosed to the centres.

All analysis programmes regarding efficacy endpoints (see section 2) will be prepared by the study statistician using a dummy treatment variable. No evaluation of efficacy endpoints by randomised treatment will be allowed before the final database lock.

## 10.3 Definition of estimands and analysis sets

For details on the definition of estimands, analysis sets defined in connection with estimands, and endpoints see section 2.

In addition, the analysis set IC (informed consent) is defined as all patients who give informed consent, and the analysis set SCF (screening failure) is defined as all patients who give informed consent but are not randomised. These analysis sets are defined for descriptive purposes according to the CONSORT statement.

## 10.4 Sample size calculation

In the pilot trial, mean $\pm$ SD relative changes (decreases) from baseline to follow-up of HRSD-24 were 62.2% $\pm$ 28.0% and 22.6% $\pm$ 71.6% for IPT-Work and TAU, respectively, data not shown). On the basis of a two-group t-test at two-sided significance level of 5%, a sample size of 62 observations per arm yields a power of 80% to detect a difference if the HRSD-24 mean relative changes from baseline at follow-up are assumed to differ by 28.0% points with a common SD of 55.0% (nQuery Version 9.2.0.0). The common SD is estimated to lie in between SDs seen in the pilot trial for IPT-Work and TAU, since IPT-Work and SP have similar treatment intensity. The means difference is considered both minimum clinically relevant and realistic since IPT is generally more effective than SP and IPT-Work is specifically tailored to depression in a work context. This calculation is conservative given that evaluation in a linear model adjusting for baseline measurement will further increase the power. Due to IPT-Work and SP group sizes (clusters) of only 4-6 participants and the fact that the interventions are directed at patients, the design effect induced by intracluster correlation is conservatively estimated as 1.04, yielding an increase to 62 $\times$ 1.04 $\approx$ 64 observations per arm. Given an anticipated drop-out rate at follow-up of 10%, 128/0.9 $\approx$ 144 patients should be randomised.

## 10.5 Methods of analysis

### 10.5.1 Descriptive statistics

Continuous data will be summarised by arithmetic mean with 95%-confidence interval (CI), standard deviation, minimum, 25% quantile, median, 75% quantile, maximum, and the number of complete and missing observations if greater than zero. If appropriate, continuous variables can also be presented in categories.

Categorical data will be summarised by the total number of patients in each category and the number of missing values if greater than zero. Relative frequencies are displayed as valid % (100 times number of patients divided by the number of patients with non-missing values). For ordered categorical data, the corresponding cumulative relative frequencies will also be shown.

Percentages of patients with missing values will be displayed where this percentage may be of special interest. This may be particularly relevant where the absolute numbers of patients and/or the absolute numbers of patients with missing values differ between treatment arms.

Questionnaires will be evaluated according to their respective manual. For scores and sub scores descriptive statistics and frequencies will be provided by intervention and time point.

Except for the analysis concerning the primary estimand, all other statistical analyses will be considered as descriptive.

#### **10.5.2 Patient recruitment, disposition of patients**

The dates of first and last informed consent, of first and last randomisation, and of the last visit of the last patient will be indicated. A flow chart according to the CONSORT statement will be given. The corresponding descriptive evaluations will be presented in frequency tables.

#### **10.5.3 Patients' baseline characteristics**

Demographic and other baseline data will be summarised descriptively in total and by treatment arm using the FAS. To capture seasonal effects, this will include the calendar month (January, February,...) in which the group therapy started.

#### **10.5.4 Trial interventions**

The number of therapy groups, the frequency of group sizes as randomised (4, 5 or 6), and the frequency of actual group sizes (which can be lower in case a patient does not start group therapy) will be presented in total, by centre and by treatment arm.

The number of attended group sessions per patient will be summarised both as continuous and as categorical variable in total and by treatment arm. The number of patients who attended a minimum number of group sessions, to be specified in the SAP, will be summarised in total and by treatment arm. In addition, the mean number and the mean percentage (out of 4, 5 or 6, or possibly fewer in case a patient does not start group therapy) of patients who attended each specific out of the ten group sessions will be presented in total and by treatment. Patients' treatment preferences at baseline and post-treatment will be evaluated descriptively.

#### **10.5.5 Concomitant treatment and medication**

The study team of the coordinating investigator will review and classify therapeutic interventions and concomitant medication as "allowed"/"not allowed" (see 5.3.1) based on corresponding listings, blinded to treatment allocation, to be provided to the study team by the CTU after database lock. The number of patients with any additional psychotherapeutic treatment throughout the study including the follow-up visit, the number of patients who took antidepressive medication or benzodiazepines not allowed during the study, as well as all concomitant medication as a whole will be presented in total and by treatment. The concomitant medications will be summarised by ATC level 3. In each table, patients will be counted once if they took at least one medication from the respective ATC level.

#### **10.5.6 Adherence of study therapists and interrater reliability**

The study team of the coordinating investigator will evaluate the adherence of study therapists to the respective manuals for IPT-Work and SP based on the 'Therapeutic Element Checklist' (Stundenbogen). It will also evaluate interrater reliability with respect to SCID-5 and HRSD-24 observed during diagnostic training of raters. The methods will be specified outside this protocol.

### **10.5.7 Analysis of primary estimand**

#### **Main estimator for estimand No. 1**

In the primary analysis, all randomised patients will be analysed as belonging to their randomised arm, regardless of any protocol deviations. The effects of SP and IPT-Work on the primary endpoint (difference of means [IPT-Work minus SP] of the relative change in HRSD-24 score from baseline to follow-up) will be estimated and tested in a linear mixed model for repeated measures (MMRM). The model will include randomised arm (IPT-Work and SP), time point (post-treatment and follow-up), their interaction, continuous HRSD-24 baseline scores and their interaction with time point as fixed independent variables and the therapy group (cluster) as random effect. The model will allow for intrasubject correlation using a compound symmetry correlation structure. The two-sided test at significance level 5% for a difference between IPT-Work and SP at follow-up will be based on the two-sided 95% confidence interval derived for the corresponding difference in least-squares means estimated the linear MMRM. The analysis assumes that missing values are missing at random (MAR), indicating that they are related to the independent variables, but not to the unmeasured outcomes themselves. No efficacy interim analysis will be performed.

#### **Sensitivity estimator for estimand No. 1**

If more than 10% of the HRSD-24 score measurements at follow-up are missing in at least one arm, a sensitivity analysis will be performed. In both arms, missing values will be multiply imputed from the SP arm of the primary MMRM. The analysis assumes that missing values are missing not at random (MNAR), and that values missing in the IPT-Work and the SP arms are similar to those observed in the SP arm. The results will be combined using Rubin's rules for multiple imputation.

#### **Supplementary analyses**

To assess the correlation among scores of patients treated in the same SP or IPT-Work therapy group, respectively, the intracluster correlation (ICC) will be estimated from the MMRM for descriptive purposes.

An exploratory analysis will be conducted to assess the consistency of the treatment effect across centres and genders using point estimates with confidence intervals and interaction terms.

### **10.5.8 Analysis of secondary estimands**

The difference of means between IPT-Work and SP with respect to the relative change in HRSD-24 score from baseline to post-treatment (estimand No. 2) will be derived from the same linear MMRM as the primary estimand.

For the binary outcomes based on the HRSD-24 score (estimands No. 3-6, remission and response), the analysis will be performed in a generalised linear mixed model with a logistic link function, to be specified in the SAP, under the assumption that missing values are missing at random. If more than 10% missing values occur in at least one arm at follow-up, a sensitivity analysis will be performed based on the multiply imputed HRSD-24 scores generated for the primary estimand, which will be used to multiply replace the corresponding missing remission/response status.

For the further secondary estimands, change from baseline (difference post-pre) will be analysed in a linear mixed model for repeated measures to be specified in the SAP.

### 10.5.9 Analysis of safety

Adverse events are described by main categories A-H (see section 7.1). The incidences of adverse events will be summarised in the SAF by treatment arm with two-sided 95% confidence intervals based on Wilson scores (without continuity correction) according to method 3 in Newcombe (1998).

The AEs will be displayed in summary tables by treatment as follows:

The total number of AEs, the minimum, maximum and mean number of AEs per patient will be calculated per main category A-H and in total.

The incidence of AEs defined by main categories A-H will be calculated as the number of patients who experienced at least one AE with the respective category A-H in percentage of the total number of patients.

Each table will be produced for the following AE-sets:

- All AEs
- All Serious Adverse Events (SAEs)

Additionally, these tables will be recalculated for AEs with onset during the treatment period and for AEs with onset after the treatment period.

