#### **4.2 Exclusion Criteria**

Patients eligible for this trial must **not** meet any of the following criteria:

1. Acute risk of suicide
2. History of psychotic symptoms, bipolar disorder, or organic brain disorders
3. A primary diagnosis of another SCID-5-CV disorder
4. Concurrent diagnosis of substance dependency
5. Antisocial, schizotypal, or borderline personality disorder (SCID-5-PD)
6. Other ongoing psychotherapy
7. Antidepressive pharmacotherapy (if not stable for at least the last 4 weeks before randomisation)
8. Serious medical condition or time restrictions interfering with participation in regular sessions
9. Current sick leave > 4 weeks
10. Applying for rehabilitation or early retirement
11. Patient without legal capacity who is unable to understand the nature, significance and consequences of the study
12. Simultaneous participation in other studies which could interfere with this study and/or participation before the end of a required restriction period. No prior randomisation in this IPT-Work trial.

13. Persons who are in a disciplinary employment relationship with a member of the study team

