## **7 Safety monitoring and documentation**

### **7.1 Definition of adverse events (AEs) and serious adverse events (SAEs)**

An AE in this study is defined as any untoward medical occurrence in a patient who has been randomised.

The following adverse events (AEs) will be documented to monitor safety of randomised patients according to one of the following categories (select main category)

- A) Worsening of psychopathological symptoms
- B) Appearance of new psychopathological symptoms

- C) Passive suicidal thoughts
- D) Active suicidal thoughts
- E) AEs related to the patient–therapist relationship
- F) AEs related to personal life
- G) AEs related to occupational life
- H) Other (i.e., non-psychopathological) AEs (e.g. influenza or fractures)

A serious AE (SAE) in this study is defined as any untoward medical occurrence that results in any of the following outcomes:

- Death
- Life-threatening situation (patient is at immediate risk of death)
- Inpatient hospitalisation or prolongation of existing hospitalisation (pre-planned hospitalisations do not have to be considered)
- Persistent or significant disability/incapacity
- Failed suicide attempt
- Other important medical event: An event that does not fit any of the other outcomes above, but may jeopardise the patient and may require medical or surgical intervention (treatment) to prevent one of the other outcomes above.

These definitions are based on a standardised questionnaire already applied in previous psychotherapy trials.

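### By-arm incidences of suicidal thoughts (AE categories C and D) can mix thoughts present at entry with emergent ones and can lose thoughts filed under another main category

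*Protocol*

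**What the plan says.** Section 7.1 gives the definition: "An AE in this study is defined as any untoward medical occurrence in a patient who has been randomised". Events are then documented "according to one of the following categories (select main category"). Category A is "Worsening of psychopathological symptoms" and B is "Appearance of new psychopathological symptoms". Category C is simply "Passive suicidal thoughts", and D is the active counterpart, also without a word about change.

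Section 7.2 has the event documented, from randomisation to study end, by the therapist or rater who hears of it first. An onset date is required. A diagnosis or symptoms are required only for the category of other AEs. Section 8.4 adds no coding beyond the section 7.1 categories.

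Section 10.5.9 builds the tables on that label: "Adverse events are described by main categories A-H (see section 7.1"). Incidence is the share of patients with at least one AE in the category, by arm in the safety set. The tables are repeated for onset during and onset after the treatment period.

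On entry, section 4.2 excludes "Acute risk of suicide", and section 7.4 describes its low-risk level by passive ideation. Section 7.4 also says that "cut-off thresholds in the HRSD-24 (Item 3 > 1) and BDI-II (Item 9 > 1) are checked". The visit schedule (Table 5) places both scales at V0, V12 (W9) and V13 (W21). Section 10.5.1 promises summaries of scores and sub scores, and section 2 states that the HRSD-24 has no subscales.

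**The concern.** Suicidality has its own monitoring section, so the plan itself treats it as a risk. The C and D incidences are the only by-arm account of suicidal thoughts that the protocol names. A reader will take them as what happened under each therapy. Two features weaken that reading.

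- **No baseline reference.** A patient who enters with passive thoughts and mentions them again in a session can be counted in C, although nothing has changed.
- **One label per event.** A worsening of depression with suicidal thoughts fits A as well as C or D. If A is chosen, the thoughts leave no trace in the C and D tables.

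The first feature adds events unrelated to treatment and the second removes events that may be related. Both make a real difference in emergent ideation harder to see. Meanwhile the trial collects two measures that can be compared with baseline, one by a blinded rater and one self-rated, and the safety section uses neither.

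**Working it through.** **No figure to reproduce.** The protocol gives no ideation rate. Section 3.3 supplies the arm size, about 72, which is the upper limit for the safety set. All rates below are assumptions that show the mechanism.

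**Step 1: can entry ideation reach C or D?** Section 4.2 does not exclude ideation short of acute risk. Sections 7.1 and 7.2 do not say that thoughts must have begun or worsened after randomisation. Section 7.4 has suicidality asked about repeatedly, so existing thoughts will come up. Nothing requires a reporter to log unchanged thoughts, and nothing tells the reporter not to.

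**Step 2: size.** Let b be the share with thoughts at entry, f the share of these recorded in C or D, and i the emergent incidence among the rest. The reported incidence is b·f + (1 − b)·i. Take i = 5% and 15%, a ratio of 3.

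With f = 1, for example at b = 0.1: 0.1 + 0.9 × 0.05 = 14.5% and 0.1 + 0.9 × 0.15 = 23.5%.

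| b | reported | ratio | difference |
|---|---|---|---|
| 10% | 14.5% vs 23.5% | 1.62 | 9 points |
| 20% | 24% vs 32% | 1.33 | 8 points |
| 30% | 33.5% vs 40.5% | 1.21 | 7 points |
| 40% | 43% vs 49% | 1.14 | 6 points |

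With f = 0.5, b = 20% gives 14% vs 22% (ratio 1.57) and b = 40% gives 23% vs 29% (ratio 1.26). With f = 0, the ratio stays at 3 for every b.

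**Step 3: the difference.** Table 3 names the risk difference as the AE summary measure. It equals (1 − b) × 10 points whatever f is, because f cancels. The fall from 10 points to 9-6 therefore comes from having patients with entry ideation in the denominator, not from recording their thoughts. What recording costs on this scale is precision. At b = 20% and 72 per arm, ignoring clustering:

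- f = 0: 4% vs 12%; standard error √[(0.04 × 0.96 + 0.12 × 0.88)/72] = √(0.144/72) = 4.5 points.
- f = 1: 24% vs 32%; standard error √[(0.24 × 0.76 + 0.32 × 0.68)/72] = √(0.400/72) = 7.5 points.

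The same 8-point difference is 1.8 standard errors in the first case and 1.1 in the second.

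**Step 4: single label.** Suppose 15% in each arm truly have emergent thoughts. If half are filed under A in both arms, C and D show 7.5% vs 7.5%: an undercount with no false difference. If half are filed under A in one arm only, they show 7.5% vs 15%. Only the second pattern creates a difference.

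**Step 5: can misfiled events be recovered later?** Section 7.2 requires symptoms only for other AEs, and no listed field would show suicidal thoughts within an event filed under A. A rule written at analysis cannot retrieve them.

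**The case against.** The strongest defence is the onset date. Thoughts correctly dated before randomisation have their onset in neither the treatment period nor the period after it, so they drop out of both onset tables. This stands, but only in part. It depends on the reporter entering the true start rather than the date of first mention, and the all-AE tables have no onset filter.

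Second, C and D exist for suicidal thoughts, so a reporter may well use them, and nothing prevents logging a worsening and the thoughts as two events. That is true, but section 7.1 does not ask for it either.

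Third, an item-level table is a detail that a protocol usually leaves to the SAP, which is not at hand. Its absence alone would be no finding. The point rests on the definition and data capture in section 7.1, which section 10.5.9 turns into a fixed counting rule.

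A reader might go further and infer that ideation is misreported by arm, because unblinded therapists often choose the label. The documents do not support that. All therapists run groups in both arms (section 3.5.4), raters are trained in AE assessment (section 3.4), and nothing shows that filing differs by arm. Nor does the protocol say how often the therapist is the first to hear of an event.

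**Conclusion.** The concern holds as a risk of dilution and undercounting. As sections 7.1 and 10.5.9 stand, the C and D incidences in the all-AE tables can mix entry ideation with emergent ideation, and can lose thoughts that occur within an event filed elsewhere.

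The size depends on two unknowns: how many patients enter with thoughts and how many of those are logged. On assumed emergent rates of 5% vs 15%, the ratio lies anywhere between 3 (none logged) and 1.62-1.14 (all logged, 10-40% at entry). The risk difference does not depend on how many are logged; it is estimated less precisely as more are. These tables are descriptive, so no test decision is affected. The issue is whether a harm that the plan singles out can be read from its own tables, and since the remedy is small it is worth making.

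**What to change.** 1. In sections 7.1 and 10.5.9, state that C and D count suicidal thoughts that began or worsened after randomisation. Add one yes/no eCRF field to every AE, asking whether suicidal thoughts were present, so that the incidence does not depend on the main category chosen.
2. In section 10.5.9, add by arm at W9 and at W21, for safety-set patients with the item assessed, the number and percentage newly above the existing section 7.4 cut-off among those not above it at V0. Do this for HRSD-24 item 3 and separately for BDI-II item 9, each with a baseline-to-visit shift table.

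The cost is one extra eCRF field, a sentence of reporting guidance and a few tables from data already collected. The items do not capture ideation that resolves between visits or patients who miss them, so the AE tables remain necessary. The section 7.4 cut-offs and all clinical management rules stay as they are.
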